### 2.12. Data Management

Data entries in REDCap will include radio buttons, checkboxes, dropdown menus, and text entry with reference range checks to reduce data-entry errors, and in the P3-EX web-based interface, dropdown menus, toggle buttons, and text entry with guided inputs and reference range checks. [name], [name], and RAs will have access to de-identified data stored in REDCap, and only [name] and [name] will have access to participant identifiers stored in REDCap. [name], [name], and an RA will have access to all data entered in P3-EX via the Supabase backend [67]. The RA will maintain P3-EX data through weekly backups stored in Microsoft SharePoint and REDCap. All study data and records will be retained in Microsoft SharePoint for a minimum of 6 years after the completion of the study to comply with institutional policy.

### 2.13. Sample Size Estimation

We conducted a power analysis using G*Power (version 3.1.9.6, Heinrich Heine University Düsseldorf, Düsseldorf, Germany) [68] to obtain a conservative usability rating of P3-EX to evaluate the primary aim of the study. We obtained the lowest observable usability score of 4.650 ± 0.759 (mean ± SD) converted from our feasibility survey study pilot data [32] to compare to the null hypothesis middle score of 4.0 on the mHealth Application Usability Questionnaire [50]. Using a one-sided Wilcoxon signed-rank (one sample case) test [69] at the significance level (α) of 0.01 and calculated effect size between the observed and middle score of Cohen’s d = 0.856, we determined that 19 physicians are required to achieve 85% power. Therefore, we will use 19 physicians to achieve 85% power (α of 0.01), and recruit two patients per physician to complete 38 patients. Using an observed attrition of 20% for patients in the study [70,71,72,73], this trial will aim to recruit 24 physicians and 48 patients (24 patients per group). Because physicians’ PA levels could influence how they perceive and rate the delivery of an ExRx [45], we aim to recruit half of the physicians who meet PA guidelines (n = 12) [44] and half who do not (n = 12).

### 2.14. Statistical Analysis

The statistical analysis plan for this trial is accessible on ClinicalTrials.gov. Statistical analyses will be conducted by [name] using Statistical Package for the Social Sciences (version 30, IBM Corp., Armonk, NY, USA) [74] with oversight from [name], [name], [name], [name], and [name], with [name], [name], [name], and [name] being blinded to group assignments. We will first use descriptive statistics and graphical techniques to ensure all test assumptions are met, including the inspection for outliers, normal distributions [75], and homogeneity of variances [76]. Missing values will be addressed using model-based approaches and/or multiple imputations when appropriate to include the entire randomized sample [77]. If normality assumptions are not met for secondary outcomes, considerations will be made to transform the data to achieve a normal distribution or use alternative non-parametric approaches such as permutated tests. An alpha level of 0.05 will be used to determine statistical significance.

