#### 2.14.2. Evaluation of the Secondary Aim

We will use the following statistical approaches to explore the preliminary efficacy of P3-EX to improve patient PA levels, CVD risk factors, and exercise adherence. A one-way Analysis of Variance will test if pre-intervention values are equal between groups, indicating if there is a need to adjust for potential covariates related to demographics, medication use, and/or pre-intervention PA level and CVD risk factor values. We will use a repeated measures two-way Analysis of Covariance using a linear mixed effects model to test patient differences in PA level and CVD risk factor changes over 12 weeks between the P3-EX and the PAVS groups, adjusting for potential covariates related to demographics, medication use, and/or pre-intervention values.

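### Two of the six people who run or oversee the analysis are not stated to be blinded, and the data-driven choices for the secondary between-arm comparisons are not said to be made on masked labels

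*Protocol article*

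**What the plan says.** **Who is blinded (protocol article, 2.14).** One person does the work: "Statistical analyses will be conducted by [name] using Statistical Package for the Social Sciences". The same sentence adds five overseers and ends "with [name], [name], [name], and [name] being blinded to group assignments".

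**Transformation and test (2.14).** Outliers, distributions and variances are inspected first. Then: "If normality assumptions are not met for secondary outcomes, considerations will be made to transform the data to achieve a normal distribution", or the team may "use alternative non-parametric approaches such as permutated tests". Missing values are handled by model-based methods, multiple imputation or both, as judged fitting.

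**Covariates (2.14.2).** A one-way ANOVA compares the arms at baseline to indicate whether adjustment is needed. The repeated-measures model is then fitted "adjusting for potential covariates related to demographics, medication use, and/or pre-intervention values".

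**Primary aim (2.14.1).** One-sided one-sample Wilcoxon tests compare physician ratings with 4.0 and 68. A mixed model compares the two tools, with delivery order and time between deliveries as potential covariates.

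**Related places.** Section 2.5.2 has the allocation held by someone outside data collection and outcome assessment. Section 4.3 says that the person who guides patients and takes most post-intervention measurements knows the arm. Section 5 intends the secondary-outcome data to power a larger trial.

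**The concern.** Blinding at the analysis stage is useful mainly where judgement is exercised after the data are in. Here that judgement covers the scale, the type of test, the missing-data method and the adjustment set. Someone who knows which arm is P3-EX could, without intending to, prefer the version that reads better for it. The investigators developed the tool under test, so this deserves attention.

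The protocol evidently thinks analysis-stage blinding worthwhile, since it blinds four people. It does not extend it to all who run or supervise the analysis, and it does not say that the choices are settled before the labels or the between-arm results are visible. Section 4.3 acknowledges the unblinded outcome assessment but not the unblinded part of the analysis team.

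At stake is the direction of the secondary estimates. They are exploratory, but they are tested at 0.05 and are meant to inform the size of the next trial.

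**Working it through.** **Step 1. Count (inputs from 2.14).** Analyst: 1. Overseers: 5. Total 1 + 5 = 6. Stated to be blinded: 4. Remainder 6 − 4 = 2. This assumes six distinct people and that the four blinded are among them. With names removed, it cannot be seen whether the analyst is one of the two.

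**Step 2. Which analyses are open to choice.**

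| Analysis | Section | Left to be settled on the data | Compares arms or tools |
|---|---|---|---|
| One-sample Wilcoxon against 4.0 and 68 | 2.14.1 | No: test and reference values fixed | No |
| Physician mixed model, P3-EX against PAVS | 2.14.1 | Slightly: two named covariates, called potential | Yes |
| Patient mixed model, changes over 12 weeks | 2.14, 2.14.2 | Yes: transformation or non-parametric test, missing-data method, covariates | Yes |

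The exposure lies mainly in the last row.

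**Step 3. Is masking stated for those choices?** Section 2.5.3 covers baseline assessment and the laboratory. Section 2.14 gives the four blinded people. Section 2.15 provides committee oversight of analysis methods. None says that the choices are made on coded labels or before between-arm results are seen. The baseline ANOVA in 2.14.2 uses the group variable by construction.

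**Step 4. What knowing the labels adds.** Let T be the signed test statistic for P3-EX minus PAVS under whichever analysis is chosen.
- Swapping the labels turns T into −T and leaves |T|, and so the two-sided p-value, unchanged.
- If the choice ignores the labels, then with no true effect and exchangeable arms T and −T are equally likely. The expected value of T is 0, so there is no directional bias.
- If the choice can depend on the labels, this symmetry no longer holds and T can be shifted towards one arm.

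Knowledge of the labels therefore adds direction. Freedom among analyses, which can enlarge |T|, exists with or without labels. Coding the arms deals with the first; only settling the analysis before between-arm results are seen deals with the second.

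**Step 5. Is the baseline-test rule harmful in itself?** Null simulation with assumed data: 4,000 runs per setting, 19 or 24 patients per arm, pre-post correlation 0.5 or 0.8, normal or log-normal values. The rule was: adjust for baseline if the baseline t-test has p < 0.05, otherwise do not. The type I error was 0.028 to 0.049. Applied mechanically, the rule did not inflate error; the exposure comes from discretion.

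No figure in the protocol depends on this point, so there is none to reproduce.

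**The case against.** **The SAP may already fix these rules.** Section 2.14 says that it is on the registry. It is not at hand here, and an article may leave such detail to it, so missing detail is not the point. What stands is what the article itself states: partial blinding beside choices that follow inspection of the data. If the SAP is stricter, 2.14 should be brought into line with it.

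**There are safeguards.** Four blinded people and a committee that discusses and validates analysis methods (2.15) both help. Neither is said to work before labels or results are visible.

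**The choices are conditional.** Transformation depends on failed normality and 2.14.2 names one model family. That is fair, but the condition leads only to considerations and the covariate list is open. Outlier handling should not be counted: the article mentions inspection and never removal.

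**A stronger reading is tempting.** A reader might infer that unblinding roughly doubles the false-positive rate. In the simulated settings of step 5, taking the smallest p-value from a menu of covariate sets, log, rank and outlier-exclusion analyses gave 0.096 to 0.127, against 0.043 to 0.056 for one fixed baseline-adjusted model. This does not measure unblinding. By step 4 the same rates would arise on a file coded A/B, and the menu includes an exclusion that the article does not state.

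**Masking cannot be complete.** Correct. Anyone who coached or assessed patients may recognise records (4.3), and choice of prioritisation strategy is recorded only for P3-EX (2.9.1).

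**Conclusion.** The point stands in limited form and is worth acting on, though it is not critical for a pilot. On the natural reading of 2.14, two of six people are not stated to be blinded, and the choices for the secondary between-arm comparisons are not said to be made on masked labels. The consequence is possible directional bias in exploratory estimates. Its size is unknown: the document allows no calculation, and no error-rate figure should be attached to it.

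Three further inferences are not supported:
- that the two people know the arms; the text only omits to say that they are blinded;
- that the analyst is one of them; the names are removed;
- that the primary usability conclusion is at risk; its one-sample tests are fixed and involve no arm comparison.

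The conclusion assumes distinct people with the four drawn from the six, and that the SAP does not already require masked or locked choices.

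**What to change.** In section 2.14:

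1. State which roles in the analysis team are not blinded.
2. Have the person who holds the allocation supply the analysis file with arm coded A/B for patients and tool coded X/Y for physicians, leaving out fields that reveal the arm where feasible.
3. For each outcome, fix the transformation or test, the missing-data method and the covariates from pooled data, or as the SAP already sets them, and not from between-arm significance tests.
4. Enter these choices in a dated log, locked before any between-arm outcome result is seen and before the code is released.

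Section 2.14.2 then needs the baseline ANOVA removed as the trigger for adjustment.

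The cost is a few sentences and a log, with no new staff or data. The downside is that masking stays incomplete for anyone who coached or assessed patients; for them the locked log is the main safeguard.

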#### 2.14.1. Evaluation of the Primary Aim

We will use the following statistical approaches to evaluate the feasibility and acceptability of P3-EX for physicians to use to prescribe exercise to patients with CVD risk factors. We will use a one-sided Wilcoxon signed-rank (one sample case) test [69] to assess whether the physician mHealth Application Usability Questionnaire ratings of P3-EX and the PAVS are above the null hypothesis middle score of 4.0 on the Likert scale [50], and whether System Usability Scale ratings are above the average score of 68/100 [78]. We will use a linear mixed effects model adjusting for the delivery order of P3-EX and PAVS and the time between delivery as potential covariates and interactions between these two covariates to assess differences in the physician usability questionnaire scores between P3-EX and the PAVS. We will use normal linear regression to determine the strength of relationships between the three domains on the mHealth Application Usability Questionnaire and usage time of P3-EX and PAVS.

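### The primary usability test is sized at one-sided alpha 0.01, but the analysis section sets alpha 0.05 without exception, so its significance threshold is not fixed

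*Protocol article*

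**What the plan says.** Section 2.13 names the test and its level together: "Using a one-sided Wilcoxon signed-rank (one sample case) test", "at the significance level (α) of 0.01". The planning values are "We obtained the lowest observable usability score of 4.650 ± 0.759 (mean ± SD") and a null of 4.0, with a stated Cohen's d of 0.856. The result is that "we determined that 19 physicians are required to achieve 85% power", and the level is repeated when the number is adopted: "Therefore, we will use 19 physicians to achieve 85% power (α of 0.01"). Allowing for 20% attrition, the recruitment targets are 24 physicians and 48 patients.

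Section 2.14, the general paragraph that introduces all the analyses, closes with "An alpha level of 0.05 will be used to determine statistical significance". It names no sidedness and sets no test apart.

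Section 2.14.1, on the primary aim, specifies the same test against the same value of 4.0: "We will use a one-sided Wilcoxon signed-rank (one sample case) test". It gives no significance level.

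Section 2.7 has a third statement that bears on success. It reads P3-EX as feasible and acceptable for physicians when overall scores are above 4.0, and mentions neither a test nor a p-value.

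**The concern.** A reader who follows section 2.13 expects the primary test to be judged at 0.01. A reader who follows section 2.14 judges it at 0.05, because the general level applies to any test without its own. No sentence in the article says which governs, or that 0.01 was used only for sizing.

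What is at stake is the meaning of a positive primary result. A one-sided p-value of 0.03, for example, is significant under section 2.14 and not significant under section 2.13. With both levels in print, the choice could be made after the result is known, which is what a prespecified level is meant to prevent.

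**Working it through.** **Inputs** (all from section 2.13): mean 4.650, SD 0.759, null 4.0, one-sided one-sample Wilcoxon signed-rank test, alpha 0.01, power 85%, N = 19, attrition 20%. The competing level, 0.05, is from section 2.14.

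**Step 1. Effect size.** d = (4.650 − 4.0)/0.759 = 0.650/0.759 = 0.856, as stated.

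**Step 2. Reproduce the plan's power at alpha 0.01.** Power of the Wilcoxon test is approximated by the noncentral t distribution with effective sample size n′ = N × ARE, where ARE is the asymptotic relative efficiency (3/π for normal data), df = n′ − 1 and noncentrality d√n′.
- N = 19: n′ = 19 × 3/π = 18.14, df = 17.14, noncentrality 0.8564 × √18.14 = 3.65, critical value 2.565. Power = 84.8%.
- With ARE = 1, power is 86.9%. The exact signed-rank test simulated on 200,000 normal samples gives 84.6%.
- The smallest N reaching 85% is 19 with ARE = 1 and 20 with ARE = 3/π, where 19 falls short only by rounding.
- Attrition: 19/0.8 = 23.75, rounded up to 24; 38/0.8 = 47.5, rounded up to 48. Both match.

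The stated design therefore reproduces at one-sided 0.01.

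**Step 3. Same calculation at the section 2.14 level** (ARE = 3/π, d = 0.856).

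| Level of the one-sided test | Power, N = 19 | Power, N = 24 | N for 85% power |
|---|---|---|---|
| 0.01 (section 2.13) | 84.8% | 93.5% | 20 (19 with ARE = 1) |
| 0.025 (if 0.05 is two-sided) | 93.0% | 97.5% | 15 |
| 0.05 (section 2.14, read literally) | 96.8% | 99.0% | 12 |

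Nineteen physicians follow from 0.01 and not from 0.05, so the 0.01 in section 2.13 is not a misprint for 0.05.

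**Step 4. Type I error.** Nominal ratio: 0.05/0.01 = 5, or 0.025/0.01 = 2.5 if 0.05 is two-sided. The signed-rank statistic is discrete, so at n = 19 the attainable exact sizes are 0.0478 and 0.0090, a ratio of 5.3.

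**Step 5. Where the conclusion changes.** Using a t approximation at the planned SD, the smallest significant mean is 4.0 + t × 0.759/√n.
- n = 19 (standard error 0.759/√19 = 0.174): at 0.01, 4.0 + 2.552 × 0.174 = 4.44; at 0.05, 4.0 + 1.734 × 0.174 = 4.30.
- n = 24 (standard error 0.759/√24 = 0.155): at 0.01, 4.0 + 2.500 × 0.155 = 4.39; at 0.05, 4.0 + 1.714 × 0.155 = 4.27.

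The sections disagree over a band of about 0.14 points at n = 19 and 0.12 points at n = 24.

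**The case against.** The case for leaving the text alone has several parts.

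- **The mismatch is on the safe side for power.** Sizing at a stricter level than the analysis uses only raises power. This stands: no participant number is wrong.
- **The disputed band is narrow.** It spans 0.12 to 0.14 points on a 1-to-7 scale, and both bars lie below the assumed mean of 4.65. This also stands and limits the practical weight, but a result inside the band would have no agreed reading.
- **0.05 is a conventional level for an exploratory trial, and 0.01 may have been a deliberate margin at the sizing stage.** Possible, but the article does not say so. What section 2.13 calls conservative is the usability rating, not the level.
- **The separate statistical analysis plan may fix the level.** It may, and it is not at hand. The point here is that the article itself prints two levels, not that something is left out.

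Two stronger readings are tempting and not supported. A reader might infer that the trial would declare feasibility at five times the planned false-positive rate. Section 2.7 ties that declaration to a score above 4.0 without a p-value, and section 2.14.1 never says that feasibility rests on significance, so the factor applies to the test and not to the declaration. The factor is also 2.5 if 0.05 is two-sided.

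A reader might also add the System Usability Scale test and compute a joint error of 1 − 0.95² = 9.75%. That assumes independence, yet the same physicians rate the same tool on both scales, and section 2.7 reports strong correlation between the first questionnaire and other usability measures. Section 2.7 also gives the two scales different conclusions (feasible and acceptable; above-average usability), not two routes to one claim.

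**Conclusion.** The inconsistency is real and should be settled before data are analysed. The primary test carries two significance levels, 0.01 where it is sized and 0.05 where it is analysed, and nothing in the article reconciles them. Taken literally, section 2.14 allows up to five times the sized type I error, and 2.5 times under a two-sided reading.

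The sample size is not invalidated and the trial is not underpowered. The harm is confined to an unfixed success bar, which matters if the observed mean falls between about 4.30 and 4.44 with 19 physicians (4.27 and 4.39 with 24).

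These figures rest on the planning mean and SD of section 2.13, approximate normality of the ratings and a t approximation for the bar. The existence of two levels rests on the text alone.

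**What to change.** In sections 2.14 and 2.14.1, state that the primary test (physicians' overall mHealth Application Usability Questionnaire rating of P3-EX against 4.0) is one-sided at alpha 0.01, as sized in section 2.13. Limit 0.05 to the remaining analyses and say whether it is one- or two-sided there. In section 2.7, say whether feasibility requires a significant result on this test or only a score above 4.0, so that the rule and the test agree. Carry the same wording into the statistical analysis plan.

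If the investigators really intend 0.05 for the primary test, the alternative is to keep section 2.14, state its sidedness, and restate the power in section 2.13 at that level (about 97% for 19 physicians if one-sided, 93% if two-sided).

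The cost is a few sentences and no extra participants. Holding to 0.01 makes the bar slightly stricter, by about 0.14 points at n = 19, and keeps about 85% power with 19 physicians and 93.5% if all 24 give ratings.

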#### 2.14.1. Evaluation of the Primary Aim

We will use the following statistical approaches to evaluate the feasibility and acceptability of P3-EX for physicians to use to prescribe exercise to patients with CVD risk factors. We will use a one-sided Wilcoxon signed-rank (one sample case) test [69] to assess whether the physician mHealth Application Usability Questionnaire ratings of P3-EX and the PAVS are above the null hypothesis middle score of 4.0 on the Likert scale [50], and whether System Usability Scale ratings are above the average score of 68/100 [78]. We will use a linear mixed effects model adjusting for the delivery order of P3-EX and PAVS and the time between delivery as potential covariates and interactions between these two covariates to assess differences in the physician usability questionnaire scores between P3-EX and the PAVS. We will use normal linear regression to determine the strength of relationships between the three domains on the mHealth Application Usability Questionnaire and usage time of P3-EX and PAVS.

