### 2.1. Trial Design

The P3-EX Feasibility Trial is a feasibility and pilot efficacy RCT with a two-arm crossover exploratory design (Figure 1). Physicians (N = 24) will be individually randomized with a 1:1 allocation ratio to deliver P3-EX to one of their patients (n = 24) and PAVS to another patient (n = 24) in random sequence. Because physicians will deliver P3-EX and PAVS to patients during their routine healthcare appointments that are scheduled in advance of their enrollment, we will not implement a washout period for physicians between their delivery of P3-EX and PAVS, but will control for potential period or carryover effects in statistical analyses.

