### 2.5. Physician Randomization

#### 2.5.1. Sequence Generation

We will use block randomization [43] to assign the ExRx delivery sequence among physicians (N = 24), stratified by those who meet the PA guidelines [44] (n = 12) and those who do not meet them (n = 12). Within each PA level, physicians will be randomly assigned to one of two delivery sequences using permuted blocks of four: (1) P3-EX followed by PAVS, or (2) PAVS followed by P3-EX. This approach aims to ensure equal allocation of the ExRx delivery sequences across PA levels to control for the potential confounding effect of physician PA levels on the primary aim of the study [45].

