### 4.2. Strengths

The P3-EX Feasibility Trial has several strengths. By contrasting the feasibility and acceptability of P3-EX to a generic approach of recommending exercise such as the PAVS, the findings effectively discern the usability and user satisfaction of P3-EX in routine medical care settings. The crossover design allows all physicians to gain exposure to both P3-EX and PAVS, which reduces potential interindividual variation in their ratings due to prior beliefs about exercise or their PA levels [45]. The trial also controls for the potential influences of past ExRx experience by recruiting physicians who do not provide written ExRx to patients, and controls for potential period or carryover effects between P3-EX and PAVS by randomizing the sequence of delivery and adjusting for these potential covariates in the statistical analyses. Regarding the efficacy of P3-EX, the trial draws on social ecological theory by targeting physician ExRx practices, influencing potential provider- and system-level determinants of patient PA levels and cardiovascular health [80]. We will also employ behavioral change techniques to target patient PA levels such as goal setting, feedback, and self-monitoring across both P3-EX and PAVS, which ensures a fair comparison and allows for exercise adherence to be depicted across the 12-week intervention period.

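### The P3-EX versus PAVS model does not clearly adjust for period and cannot control carryover, although the protocol claims control of period or carryover effects

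*Protocol article*

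**What the plan says.** Section 2.1 (Trial Design) of the protocol article states that "we will not implement a washout period for physicians between their delivery of P3-EX and PAVS", because appointments are booked before enrolment. It adds that the investigators "will control for potential period or carryover effects in statistical analyses". Section 4.2 (Strengths) presents this control as a property of the trial, obtained by "randomizing the sequence of delivery and adjusting for these potential covariates in the statistical analyses".

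The analysis is in Section 2.14.1. It is a linear mixed effects model for the difference in physician usability scores between P3-EX and PAVS, "adjusting for the delivery order of P3-EX and PAVS and the time between delivery as potential covariates and interactions between these two covariates". No term is called period or carryover, and neither covariate is crossed with the prescription method. The text does not say how delivery order is coded.

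Section 2.5.1 describes the randomisation: "physicians will be randomly assigned to one of two delivery sequences using permuted blocks of four", namely P3-EX then PAVS or the reverse. This is done within two strata of 12, so 12:12 is the planned balance.

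**The concern.** A period effect is a shift between a physician's first and second delivery, whichever method comes first. Here it is plausible: physicians do not practise with either method beforehand (Section 2.4), there is no washout, and each method is rated within 48 hours of use (Section 2.7). To adjust for it, the model needs a term that differs between a physician's two ratings. Delivery order in the sense of Section 2.5.1 is a property of the physician, as are the gap and the product of the two.

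Carryover is a separate matter. If using P3-EX first changes the later PAVS rating by more or less than the reverse, that difference lies inside the within-physician contrast. In a two-period, two-sequence design no covariate in the model takes it out.

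At stake are the precision of the P3-EX versus PAVS comparison (and its bias if the sequences end up unequal), and the accuracy of a stated strength of the design.

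**Working it through.** **The plan's own figure.** Section 2.13 gives d = (4.650 − 4.0)/0.759 = 0.856 and 19 physicians for 85% power at one-sided alpha 0.01. A one-sample t-test at n = 19 has 86.9% power. A Wilcoxon test with normal-parent efficiency 3/π has 84.8%. Then 19/(1 − 0.2) = 23.75, so 24. The figure is reproduced, and it does not involve the crossover model.

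**What the listed terms do.** Let D be a physician's P3-EX score minus PAVS score, τ the method effect, π the period effect (second minus first), and λ the carryover after P3-EX minus the carryover after PAVS. Setting carryover after PAVS to zero for simplicity:
- P3-EX first: E(D) = τ − π − λ
- PAVS first: E(D) = τ + π

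Sequence, gap and sequence-by-gap take the same value in both of a physician's ratings, so they cancel from D. With complete pairs the method estimate is the plain mean of D, with or without them.

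One simulated 12:12 data set confirms this. Its assumptions are τ = 0.3, π = 0.5, no carryover, between-physician SD 0.60, within-physician SD 0.46 and gap uniform on 0–8.

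| Model | Method estimate | SE |
|---|---|---|
| method only | 0.2576 | 0.1327 |
| + sequence, gap, sequence-by-gap | 0.2576 | 0.1327 |
| + period | 0.2576 | 0.1174 |
| + first/second position, gap, position-by-gap | 0.2564 | 0.1206 |

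The last row is the alternative coding of delivery order; period is then adjusted for.

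**Cost of omitting period at 12:12.** The two sequence means average to τ, so there is no bias. The spread between them enters the estimated variance of D, which becomes 2σ² + π² × 24/23, where σ is the within-physician SD of one rating. The documents give neither σ nor π. I take σ = 0.54 (0.759/√2 = 0.537, a correlation of 0.5 between a physician's two ratings) and, as an alternative, 0.46.

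| σ | π | SE without period | SE with period |
|---|---|---|---|
| 0.54 | 0 | 0.156 | 0.156 |
| 0.54 | 0.25 | √(0.6484/24) = 0.164 | 0.156 |
| 0.54 | 0.5 | √(0.8441/24) = 0.1875 | √(0.5832/24) = 0.156 |
| 0.46 | 0.5 | √(0.6841/24) = 0.169 | √(0.4232/24) = 0.133 |

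At σ = 0.54 and π = 0.5 the inflation is 0.1875/0.1559 = 1.20. In simulation with σ = 0.46, τ = 0.3 and π = 0.5, power at two-sided 0.05 was about 37% without a period term and 58% with it.

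**Bias under imbalance.** Without a period term, the bias has size π × (difference in sequence counts)/N. For π = 0.5:
- 10:9: 0.5 × 1/19 = 0.026
- 11:8: 0.5 × 3/19 = 0.079
- 12:7: 0.5 × 5/19 = 0.132

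The bias halves for π = 0.25. Its sign depends on which sequence loses physicians. With a period term it is zero.

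**Carryover.** Averaging the two sequence means gives τ − λ/2. In simulation at 12:12 with π = 0.5 and λ = 0.5, the bias was −0.25 both with and without a period term.

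**The case against.** The strongest reply is that the coding is not stated. If delivery order means first or second position, it is the period term, and a statistical analysis plan that is posted but not shown here may say so. This stands as far as period goes: that period is left unadjusted follows from the natural reading of the text and is not stated in it. It does not rescue the carryover claim, which fails under both codings.

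Second, Section 4.2 relies on randomised sequence as well as on adjustment. That also stands: at 12:12 randomisation alone removes period bias. A reader might infer that the comparison is biased as planned, and the documents do not support that. An ignored period effect at balance makes the standard error too large and the test conservative.

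Third, sequence imbalance is not something the plan predicts. The 20% attrition in Section 2.13 is stated for patients, while physicians rate within 48 hours of delivery, so a patient lost later in the 12 weeks does not remove a physician's rating. The plan does allow for 19 physicians, but nothing points to 11:8 or 12:7.

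Fourth, the cancellation holds for complete pairs. If a physician gives only one rating, a mixed model also draws on between-physician information and the order terms can matter.

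Finally, P3-EX is judged feasible by one-sample tests against 4.0 and 68, which do not use this model, and Section 2.1 calls the design exploratory. A reader who took this point to undermine the feasibility conclusion or the sample size would be going beyond it.

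**Conclusion.** The point holds as a mismatch between a stated claim and a stated model, and should be corrected. On the natural reading, the model has no term that adjusts for period; on the other coding it does. On either, differential carryover remains, at half its size, and the claim to control it should not stand.

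The consequence for period is limited. At 12:12 it is a loss of precision: about 20% on the standard error for an assumed 0.5-point period effect with σ = 0.54, about 5% for 0.25 points (0.164/0.156), and none at zero. Bias from period needs unequal sequences, and for 0.5 points it ranges from about 0.03 (10:9) to 0.13 (12:7). These sizes rest on a period effect and a within-physician SD that the documents do not give; the cancellation and the half-size carryover bias do not depend on those values.

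It would also be wrong to infer that adding a sequence term cures carryover. Such a term can at most test for it between physicians, weakly with 19 to 24 of them, and leaves the within-physician contrast unchanged.

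**What to change.** In Section 2.14.1, define the model as score = method + period (first or second delivery) + sequence, with a random physician effect. Let the time between deliveries act through gap-by-period in place of the order-by-gap term.

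Add a sensitivity analysis comparing first deliveries only, between physicians, which is free of carryover. Label it as low in precision: if the pilot SD of 0.759 applied to both methods, its standard error at 12 v 12 would be 0.759 × √(1/12 + 1/12) = 0.31, about twice the 0.156 of the within-physician contrast.

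Reword Sections 2.1 and 4.2 to say that period is adjusted for, and that carryover cannot be removed by the model and is only examined in that sensitivity analysis.

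The cost is wording and one degree of freedom for period. Keeping gap-by-period uses one more within physicians; in the simulated 12:12 data set the standard error moved from 0.1174 to 0.1206. If there is no period effect, the standard error at 12:12 is essentially unchanged. No further physicians or patients are needed.
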